##### Safety

Safety data will be evaluated descriptively, including all randomized study patients, who received at least one dose of study medication and/or underwent surgery (safety population).

##### Methods for additional analyses, such as subgroup analyses and adjusted analyses

Additionally, logistic regression analyses of the primary endpoint adjusted for tumor size (Koos classification and volumetry), preoperative hearing, extent of resection, positioning of the patient during surgery (semi-sitting or supine), total dose of nimodipine, dose modification (yes/no), and intraoperative events, e.g., bleedings (yes/no), as well as subgroup analyses by the following subgroups are planned:
Preservation of cochlear nerve intraoperative by surgeons’ statement (yes/no)Cystic tumor by blinded expert evaluation (yes/no)SexBAEP (amplitude and latency: stable/worsened/totally lost)

## Methods: monitoring

### Data monitoring

As a measure of quality control, risk-adapted on-site data monitoring is conducted during the enrolment period by independent clinical monitors from the CCT Halle to ensure patient safety, adherence to protocol and GCP, and consistency of the data. This is done according to GCP and standard operating procedures (SOP). The specific extent of the monitoring and source data verification is specified in the monitoring manual. In addition, regular central data monitoring via electronic CRF will be performed during the study course to check the data quality in a continuous manner. Every trial site will undergo a close-out visit by the monitors after the last participant at that site has finished the follow-up. To ensure the quality of data and study performance, the sponsor may conduct site visits by an independent auditor.

An independent Data Safety Monitoring Board (DSMB) is established to monitor safety data during the course of the clinical trial. The composition (neurosurgeon, ENT, biostatistician) and responsibilities of the DSMB and the structure and procedures of its meetings are laid down in the DSMB charter.

#### Interim analysis

An interim analysis is planned for the time point when half of the patients (168 patients) have been randomized and their primary endpoint has been evaluated. The study design includes a two-stage design with interim analysis at information fraction 0.5 with O’Brien-Fleming-type alpha-spending and possible trial stop because of futility.

### Harms

Adverse events, e.g., any untoward medical occurrence in a subject without regard to the possibility of a causal relationship, occurring from the day before surgery until hospital discharge will be captured according to GCP and common standards. Any event meeting criteria of a serious adverse event will additionally be immediately reported to the sponsor according to legal regulation. Further expedited reporting to the competent authority, the relevant ethics committee, and all investigators are done in case of a suspected unexpected serious adverse reaction. For classification of the adverse events, the MedDRA code system will be used.

Any pregnancy that occurs during trial participation must also be reported.

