#### Interventional group

Patients assigned to the interventional group will receive nimodipine parenterally from the day before surgery until the 5th postoperative day additional to surgery as standard care. Nimodipine should be given as soon as possible on the day before surgery. However, due to the clinical situation, a defined time was not determined. Administration of nimodipine will be started via a peripheral venous access with a dosage of 1 mg/h (5 ml/h) for at least 2 h. If nimodipine is well tolerated, the dosage should be increased to 2 mg/h (10 ml/h). During and after surgery, nimodipine should be administered via a routine central line. Blood pressure should be monitored three times a day due to the effects of and on nimodipine. In case of hypotension, a dose reduction of 1 mg/h or 0.5 mg/h or a stop of treatment is intended. The administration of nimodipine and thus the cumulative dosage will be documented for each patient. Afterward, until the patient’s end of study, nimodipine treatment is not permitted except in case of emergency of aneurysmal SAH.

Nimodipine will be purchased by Bayer Vital GmbH, Leverkusen, Germany.

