### Participant timeline

Duration of intervention: 7 days

Duration of follow-up: 3 to 6 months

Study related: estimated start 4th quarter 2020. Duration of enrolment: 21 months, interim analysis, 21 months. Estimated end of the trial: 2025

A detailed visit schedule and trial flow chart is provided (Figs. 1 and 2). The schedule lists all of the evaluations in tabular form and indicates with an “X” when they have to be performed.

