### Statistical methods

#### Populations for analysis

The primary analysis data set is the modified intention-to-treat population. This data set contains all the patients who have been enrolled in the clinical trial, randomized, and treated by surgery with pre- and postoperative values of the nervus cochlearis and tumor size.

The secondary analysis data set is derived from the per-protocol population. This data set includes all patients of the primary analysis data set without major inclusion/exclusion violations who have been treated according to their randomization schedule: For patients in the nimodipine group, this requires nimodipine treatment at least 18 h per day (with any dosis) from day −1 (day before surgery) until day 5 after surgery (in total 7 days); patients in the control group having received nimodipine will be excluded.

The tertiary analysis data set (safety population) contains all the patients who underwent surgery and/or received at least one dose of the study medication.

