## Discussion

This randomized, two-armed, multi-centric phase III trial will investigate the efficacy and safety of prophylactic nimodipine for hearing preservation in VS surgery. The treatment in the control group is active standard medical care. Nimodipine is primarily used in SAH for more than 20 years. Except for dose-depending hypotension, nimodipine is a safe drug. Severe harms to the participants are not expected; however, all patients undergo a comprehensive clinical monitoring during trial participation including 3 to 6 months of follow-up after the end of study treatment. Thus, the potential benefit of the prophylactic treatment for hearing preservation and thus communication abilities in the professional and private life of the participants is considered to be much higher than the risk of potential side effects.

In principle, prophylactic treatment with neuroprotective drugs prior to interventions with nerve tissue at risk seems to be a novel and promising concept and may have influence on basic research (investigation of the underlying molecular mechanisms). The patients of the control group will not receive neuroprotective nimodipine treatment. In the first phase III trial, an intraoperative start of the medication was allowed in the control group [15]. This might be the reason for the missing significant effect of the treatment. In the clinical course, nimodipine is occasionally given as an off-label-use medication; however, the medication is not being applied at many neurosurgical departments in Germany. There are no recommendations for perioperative nimodipine treatment in the guidelines for VS surgery; thus, the treatment of the control group represents the international standard of care. Therefore, the approach with different treatments (preoperative nimodipine versus no medication) in the intervention and the control group is justified from an ethical point of view as well as to address the scientific question in an appropriate way. A double-blind design, usually the favorable approach in clinical research, has not been proven as feasible for the reasons described in the “Blinding” section.

Therefore, nimodipine will be administered parenterally via a routine central line from the day before surgery until the fifth postoperative day exclusively in the treatment group. The chosen dosage of 1–2 mg/h is the standard dosage of nimodipine in the treatment of aneurysmal SAH patients.

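### Adverse event capture ends at hospital discharge, not on a fixed day, so observation windows may differ by arm and do not clearly reach the follow-up cited for safety

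*Protocol article*

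**What the plan says.** Harms sets the same start and the same closing event for both arms: adverse events "occurring from the day before surgery until hospital discharge will be captured according to GCP and common standards". It names no calendar day. The sentence on serious adverse events requires immediate reporting and has no end date of its own. Pregnancies are to be reported throughout trial participation.

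Under Interventional group, patients "will receive nimodipine parenterally from the day before surgery until the 5th postoperative day additional to surgery as standard care", and "During and after surgery, nimodipine should be administered via a routine central line". Participant timeline gives "Duration of intervention: 7 days". The per-protocol definition requires at least 18 hours of infusion per day "until day 5 after surgery (in total 7 days". Under Control group, patients are managed according to each site's routine, with no minimum stay. Under Blinding, five postoperative days with a central line are treated as an extra burden that a placebo would place on controls.

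The Safety section plans a descriptive evaluation of everyone operated on or dosed. The Discussion supports its risk-benefit statement partly by saying that "all patients undergo a comprehensive clinical monitoring during trial participation including 3 to 6 months of follow-up after the end of study treatment".

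**The concern.** Two things do not fit together.

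First, the safety window closes at an event that the allocated treatment can influence. A continuous central-line infusion planned to postoperative day 5 tends to keep a patient in hospital until then. Nothing comparable holds a control patient, and discharge is decided with the arm known. If controls leave earlier, the nimodipine arm is observed for longer and will show more events even if the drug causes none. Safety is part of the stated objective and is listed among the secondary outcomes, and no common window or allowance for observation time is mentioned.

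Second, the Discussion draws reassurance from months of follow-up for which Harms sets out no routine adverse event capture. A reader of the results could take an absence of late events as evidence, when such events may simply not have been collected. This second point would remain even if both arms left hospital on the same day.

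**Working it through.** **Reproducing the plan's figure.** Counting days −1, 0, 1, 2, 3, 4 and 5 gives 7 days. This agrees with Participant timeline and with the per-protocol definition.

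**How window length feeds into event counts.** The documents give neither discharge days nor event rates, so the inputs here are assumptions:

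- no drug effect, and the same constant daily risk in both arms;
- 20% of patients have at least one event in 5 days;
- nimodipine patients leave on day 5, giving a window of 7 days (day −1 to day 5);
- controls leave 0, 1 or 2 days earlier, giving windows of 7, 6 or 5 days.

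The probability of at least one event in a window of w days is 1 − 0.8^(w/5).

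| Control window | Nimodipine window | Ratio of days | Controls with an event | Nimodipine with an event | Artefact |
|---|---|---|---|---|---|
| 7 days | 7 days | 1.00 | 26.8% | 26.8% | 0 points |
| 6 days | 7 days | 1.17 | 1 − 0.8^1.2 = 23.5% | 26.8% | 3.3 points |
| 5 days | 7 days | 1.40 | 20.0% | 1 − 0.8^1.4 = 26.8% | 6.8 points |

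Under these assumptions the nimodipine arm has 0 to 40% more observation time, and the artefact is 0 to about 7 points. The upper end needs controls to leave on postoperative day 3. It would be larger with a wider gap or a higher daily risk, and smaller if events cluster around surgery, which both windows cover. With one fixed window for both arms the ratio is 1.00 and the artefact is zero by construction.

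**How much of the follow-up lies after discharge.** Assume discharge between day 5 and day 10 and a follow-up visit at 3 to 6 months (30.44 days per month). The share of postoperative follow-up after the capture window closes is then between 1 − 10/91.3 = 89% and 1 − 5/182.6 = 97%.

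**Harms beside the Discussion.** Harms extends only pregnancy reporting explicitly to the whole of participation. The serious adverse event sentence presents immediate reporting as an addition to the capture just described. It can therefore be read as bound to the same window or as open-ended. The Discussion cites the full 3 to 6 months. The text does not say which adverse events, if any, are asked about in that time.

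**The case against.** **Nothing shows that the windows differ.** A reader might infer that harms will in fact be counted over unequal windows. The documents do not support that. They state no length of stay for either arm, nimodipine may be discontinued early, and if both arms routinely leave at the same time on or after day 5 the windows are equal. This stands: unequal windows are a foreseeable risk of the rule, not an established fact.

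**The follow-up is not empty of safety information.** A reader might also conclude that it yields no adverse event data at all. That goes too far. Pregnancies are reported throughout, the serious adverse event sentence is undated, and the safety board monitors during the course of the trial. What remains is that routine capture after discharge is not provided for and capture of serious events is ambiguous.

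**Capture to discharge covers the planned exposure.** This is true for patients who stay until the infusion ends, and how long to collect events afterwards is a design choice. The Discussion also speaks of clinical monitoring rather than event recording, and relies on long experience with the drug as well. That weakens the contradiction. It does not remove the mismatch, because the follow-up period is still offered as a reason for reassurance.

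**Blood pressure.** The line "Blood pressure should be monitored three times a day due to the effects of and on nimodipine" stands only under the interventional group, and a reader might infer that hypotension is looked for in one arm only. The text cannot establish this. The line belongs to a description of drug administration, controls follow site routine, and the visit schedule is a figure that is not shown. It forms no part of this point.

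**This is a condensed article.** Detail may sit in the full protocol. The article nevertheless states a definite closing rule, and that rule is what is questioned here.

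**Conclusion.** The point holds in a limited form. Capture ends at discharge rather than on a fixed day, and the regimen gives one arm only a reason to stay through postoperative day 5. Observation windows may therefore differ by arm, and a longer nimodipine window would inflate that arm's event count. The size cannot be determined from the documents. It is zero if discharge days match, and about 7 points is only the upper end of an assumed 0 to 7 point range resting on a 20% five-day risk, a constant daily risk and a gap of up to two days.

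Separately, and whatever the discharge days, routine adverse event capture does not clearly reach the 3 to 6 months that the Discussion cites. The primary efficacy analysis is not affected. The safety comparison, which serves a stated objective, is.

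**What to change.** 1. In Harms, replace discharge as the closing point with the same fixed number of days after surgery in both arms, applied regardless of discharge and long enough to cover the planned infusion. Compare the arms over that window.
2. If that cannot be adopted, report the length of the capture window and exposure-adjusted event rates by arm. This is second best: if events cluster around surgery, the extra days in a longer window carry little risk, and a simple rate per day would then favour the arm observed for longer.
3. State explicitly that serious adverse events are captured through the existing 3 to 6 month visit in both arms.
4. Reconcile the Discussion with Harms, so that the risk-benefit statement claims only the safety information that is actually collected.

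The cost is a protocol amendment and slightly more event documentation, including contact with patients who leave before the fixed day. The later visit already takes place. If the full protocol already fixes a common window and an end date for serious events, only the article's wording needs correcting.

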### Auditing

In compliance with the International Conference on Harmonization (ICH)-GCP guidelines, audits may be performed as a quality measure by the sponsor or an independent external party, as well as inspections by regulatory authorities. For quality control by regular monitoring, please refer to the “Data monitoring” section.

### Ancillary and post-trial care

For all patients participating in this trial, an insurance covering trial-related harms is contracted according to national law. Post-trial care of VS will be the investigator’s discretion and done according to the German treatment guidelines/clinical routine.

#### Protocol amendments

Substantial amendments to the protocol according to definitions in national law have to be submitted by the sponsor and to be approved by the Competent Authority and Ethics Committees before being implemented. Only changes of the protocol that are required for patient safety may be implemented prior to approval.

### Dissemination policy

The trial is registered with full description at the German Clinical Trials Register (Deutsches Register Klinischer Studien, DRKS).

The results of the trial will be published independent of the size or direction of the effects, according to CONSORT guidelines, in peer-reviewed national and international journals with a special emphasis on media that is relevant for professionals in Neurosurgery. Additionally, clinical trial summary results will be published in the European Union Clinical Trials Database (EudraCT).

## Discussion

This randomized, two-armed, multi-centric phase III trial will investigate the efficacy and safety of prophylactic nimodipine for hearing preservation in VS surgery. The treatment in the control group is active standard medical care. Nimodipine is primarily used in SAH for more than 20 years. Except for dose-depending hypotension, nimodipine is a safe drug. Severe harms to the participants are not expected; however, all patients undergo a comprehensive clinical monitoring during trial participation including 3 to 6 months of follow-up after the end of study treatment. Thus, the potential benefit of the prophylactic treatment for hearing preservation and thus communication abilities in the professional and private life of the participants is considered to be much higher than the risk of potential side effects.

In principle, prophylactic treatment with neuroprotective drugs prior to interventions with nerve tissue at risk seems to be a novel and promising concept and may have influence on basic research (investigation of the underlying molecular mechanisms). The patients of the control group will not receive neuroprotective nimodipine treatment. In the first phase III trial, an intraoperative start of the medication was allowed in the control group [15]. This might be the reason for the missing significant effect of the treatment. In the clinical course, nimodipine is occasionally given as an off-label-use medication; however, the medication is not being applied at many neurosurgical departments in Germany. There are no recommendations for perioperative nimodipine treatment in the guidelines for VS surgery; thus, the treatment of the control group represents the international standard of care. Therefore, the approach with different treatments (preoperative nimodipine versus no medication) in the intervention and the control group is justified from an ethical point of view as well as to address the scientific question in an appropriate way. A double-blind design, usually the favorable approach in clinical research, has not been proven as feasible for the reasons described in the “Blinding” section.

Therefore, nimodipine will be administered parenterally via a routine central line from the day before surgery until the fifth postoperative day exclusively in the treatment group. The chosen dosage of 1–2 mg/h is the standard dosage of nimodipine in the treatment of aneurysmal SAH patients.

Since it has been shown that there is no significant change in cochlear nerve function between the early postoperative course and 1 year after VS surgery [25], a potential hearing loss from fluid in the mastoid/middle ear in the early postoperative course should not affect the substance of the findings.

Prophylactic parenteral nimodipine treatment may have a positive effect on hearing preservation in VS surgery and would significantly improve patient’s quality of life. Additionally, social and rehabilitation costs may be reduced when preservation of hearing can be achieved by prophylactic neuroprotective treatment. Therapy costs of nimodipine treatment are assumed to be considerably lower compared to individual rehabilitation measures on patients suffering from reduced hearing or even hearing loss. In the future, prophylactic nimodipine treatment may be recommended as a routine medication in VS surgery and possibly in other surgical procedures with nerves at risk.

## Trial status

Protocol version: AkniPro 2 V03F July 13, 2020

Study dates: Recruitment phase: January 2021 to January 2025 (planned)

Follow-up phase: May 2021 to May 2025

## Data Availability

All study-related information will be stored securely at the study site. Each trial site will have access to their eCRF data and receive a copy after closed data base. The sponsor has access to the complete data set of the trial. The regulations of the Data Protection laws will be complied with. It will be assured by the sponsor that all investigational materials and data will be pseudonymized before scientific processing.

## Abbreviations

AAOHNS: American Academy of Otolaryngology-Head and Neck Surgery
BAEP: Brainstem audiometry evoked potential
CCT Halle: Coordination Centre for Clinical Trials, University of Halle (Saale)
CONSORT: Consolidated Standards of Reporting Trials
DRKS: Deutsches Register Klinischer Studien
DSMB: Data Safety Monitoring Board
eCRF: Electronic Case Report Form
ENT: Ear, nose, and throat
EudraCT: European Union Clinical Trials Database
GCP: Good Clinical practice
GR: Gardner-Robertson scale
HHIE: Hearing Handicap Inventory for the Elderly
ICH: International Conference on Harmonization
ID: Identification
ISO: Organization for Standardization
i.v.: Intravenous
MRI: Magnet resonance imaging
PANQOL: Penn Acoustic Neuroma Quality of Life
PTA: Pure-tone average
SAH: Subarachnoid hemorrhage
SPL: Sound pressure level
SRT: Speech reception threshold
SF: Short Form
VS: Vestibular schwannoma
WRSmax: Word Recognition Score
